**Focus groups**			
	Selection of index cases and relatives	A purposeful sample of index cases and relatives accepting participation in focus groups will be selected by the qualitative methodologist and the PI.	Characteristics of index cases invited in the focus groups (preferred language, gender, mutation, type of cancer). Characteristics of families invited in the focus groups (level of support and communication).
	Invitation letters for focus groups	The PI in collaboration with the qualitative methodologist will send invitation letters initially to index cases and then to families selected for the focus groups.	Acceptance rate.
	Focus groups	Focus groups are organized and completed under the auspices of the qualitative methodologist.	Narrative data from focus groups.

Characteristics of the target populations.Inclusion criteriaLiving carriers of germline pathogenic variants associated with HBOC and LS, and their relatives (1st and 2nd degree, and 1st cousins)Have at least one living blood relativeBoth gendersAge ≥18 years oldMentally/physically able to provide informed consentCancer patients and cancer-free individualsCan read/speak German or French or Italian or EnglishCurrently living in SwitzerlandExclusion criteriaCarriers of unclassified genetic variants in *BRCA1, BRCA2* or *MLH1, MSH2, MSH6, PMS2, EPCAM* genesCurrently not living in SwitzerlandCritically ill patients not able to complete the surveyNot able to provide an informed consentInstitutionalized (eg, nursing homes) or incarcerated

**Figure 1 figure1:**
[figure not shown]
Expected recruitment of index cases.

Estimates of sample size are based on the PI’s experience, consultations with medical directors of clinical sites, and assuming average prevalence rates of 5% for hereditary breast cancer and 2-5% for hereditary colorectal cancer (the two most common manifestations of HBOC and LS), respectively. Assuming that is feasible to recruit 10% of mutation carriers from each participating clinic, 300 index cases will be targeted for inclusion within 12 months. It is expected that around 70% of approached index cases will accept participation, meaning that 495 index cases need to be approached to reach 305. It is estimated that from each index case we will identify 2.5 relatives. Assuming a response rate of 50% among relatives, we expect to recruit approximately 381 relatives. Figure 1 presents the CONSORT [68] diagram for recruitment of expected index cases and relatives.

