Index cases will be mailed an information letter, two copies of the informed consent form, two copies of a participation refusal form, and a stamped self-addressed envelope to return their response to the clinical site. Index cases will be informed about the objectives of the CASCADE study, participation requirements, the study plan, confidentiality, and associated risk and benefits through the informed consent form, which explicitly requires their agreement to (1) complete the CASCADE survey, (2) contact one or more of their blood relatives for the study, (3) be contacted once a year for 5 years and provide updated information about their health, and (4) participate alone or with a blood relative in a focus group. Index cases can participate in all or in some of the above study steps. The information letter explains that the minimum requirement for taking part in the CASCADE study is to complete the self-administered survey once. The refusal form asks nonparticipating index cases the reason for their refusal; this information is necessary for the validity of the study.

Site coordinators will determine whether the identified index case can be contacted or not by investigating whether they are alive and whether they live in Switzerland through hospital and civil records. If the recruitment package is returned undelivered, additional address verification methods will be used to locate a new residence. If the index case cannot be contacted a priori, coordinators will determine whether a first-degree relative can be the new index case for the family. Three attempts will be made to contact index cases for each family. If the study receives no response 6 weeks after the third attempt, a new family will be selected to preserve required sample size. Index cases will be recruited to the CASCADE study on a consecutive ongoing basis. Site coordinators will review pedigrees and family history of index cases who accept participation to extract demographic and medical information and to record all blood relatives (first- and second-degree relatives and first cousins). Index cases will be asked to complete a self-administered survey.

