### Recruitment Procedures for Relatives

In order to alleviate ethical concerns associated with contacting blood relatives (ie, first- and second-degree relatives, and first cousins) without their explicit consent, the CASCADE study will approach them through index cases and will approach only relatives the index case is willing to contact. This recruitment method has been used in previous family-based studies with very good recruitment outcomes [69,70]. Index cases will be mailed recruitment packages to pass on to their relatives, including an information letter, two copies of the informed consent form, two copies of the participation refusal form, and a stamped self-addressed envelope for relatives to return their response to the PI. Relatives’ identifiable information will not be released to the PI. By returning a signed informed consent, the relative indicates willingness to participate and releases their identifiable information to the PI. Once this information is available, a recruiter will contact them to ascertain eligibility. If relatives do not respond after 6 weeks, the PI will contact the index case asking them to pass on a reminder letter to the nonresponding relative. If this effort yields no response, there will be no further attempts to contact the relative. Relatives agreeing to participate will receive a similar survey as the index case, asking if they are willing to (1) invite additional relatives to the CASCADE study, (2) be contacted once a year for 5 years and provide updated information about their health, and (3) participate alone or with a blood relative in a focus group. Relatives can also participate in all or some of the above study steps.

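### The planned 70% acceptance, 495 index cases approached and 305 recruited do not agree: 305 at 70% acceptance needs 436 approached

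*Protocol article*

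**What the plan says.** All the planning figures stand in one paragraph of the protocol article, under Methods, Sample and Sample Size, next to Figure 1.

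- Target: "300 index cases will be targeted for inclusion within 12 months".
- Acceptance and number to approach, in the next sentence: "It is expected that around 70% of approached index cases will accept participation, meaning that 495 index cases need to be approached to reach 305".
- Relatives per index case: "It is estimated that from each index case we will identify 2.5 relatives".
- Relatives recruited: "Assuming a response rate of 50% among relatives, we expect to recruit approximately 381 relatives".

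The paragraph refers to Figure 1 for the expected recruitment flow. That figure is not reproduced in the text available for this review.

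**The concern.** The sentence is written as a derivation: an acceptance rate goes in, and the number to approach comes out as its consequence. A reader who repeats the division does not get 495. The target also moves from 300 to 305 between two adjacent sentences without explanation.

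The Outcomes section lists the response rates of index cases and relatives among the measures of registry feasibility, and this paragraph gives the only expected values for them. As written, a study that approached 495 and enrolled 305 would match its planned counts and miss its planned rate, so a later report could not say cleanly whether recruitment went as expected. The number to approach also determines site workload, because each index case may be contacted up to three times.

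**Working it through.** **Inputs** (all from the sample size paragraph): acceptance 70%; approached 495; yield 305; target 300; 2.5 relatives per index case; 50% response among relatives.

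**1. Trying to reproduce 495.** Number to approach = yield / acceptance rate.

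- For 305: 305/0.70 = 435.7, so 436.
- For 300: 300/0.70 = 428.6, so 429.
- With the common slip of adding 30% instead of dividing by 0.70: 305 × 1.30 = 396.5 (397); 300 × 1.30 = 390.

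None of these is close to 495. The excess over the correct figure for 305 is 495 − 436 = 59, and 59/436 = 13.5%.

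**2. Does the word "around" cover the gap?**

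| Acceptance | Approaches needed for 305 |
|---|---|
| 75% | 407 |
| 70% | 436 |
| 65% | 470 |
| 61.6% | 495 |

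Even 65% falls short of 495. The rate that gives 495 is 305/495 = 61.6%.

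**3. Working forward from 495.** 495 × 0.70 = 346.5, so about 346 index cases rather than 305.

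**4. What would reconcile all three figures.** A second factor of 305/346.5 = 0.88, that is, a further loss of about 12% in addition to the 30% who decline. The paragraph mentions none.

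**5. The relatives' line.** 305 × 2.5 × 0.50 = 381.25, which reproduces 381. With 300 index cases the same product is 375. So 381 is consistent with 305, and it does not use 495.

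**The case against.** **A missing loss step.** The strongest defence is that Figure 1 may show an intermediate loss, such as cases that could not be reached, which takes 495 down to 305. That is possible, and it is why the text alone cannot show whether 495 or 70% is the wrong figure. It does not rescue the sentence, which applies the 70% to approached cases and presents 495 as its consequence. The section on recruitment of index cases also settles living status and residence before anyone is invited, and replaces an unavailable case by a carrier relative or by the next family. Some packages may still come back undelivered, but the article gives no rate for this.

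**Little depends on 495.** This stands. Nothing else in the text is calculated from it, and a new family is drawn after non-response, so recruitment is not capped at 495. If 70% is right, the slip plans too many approaches rather than too few. The difference between 300 and 305 is under 2% and is untidy rather than material.

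**A stronger reading of the relatives' figure.** A reader might infer that 381 assumes that every index case agrees to invite relatives, because "Index cases can participate in all or in some of the above study steps" and the study "will approach only relatives the index case is willing to contact". The documents do not support that. The 2.5 is an average per index case and can include index cases who invite nobody. Table 1, in its row on identifying eligible relatives, describes them as those whom the index case is willing to invite. On that wording willingness is already inside the 2.5. Discounting 381 by an assumed opt-in of 60% to 80% (229 to 305 relatives) would use a share found nowhere in the article and might count refusal twice. What remains is a matter of clarity: the Outcomes section lists relatives identified from pedigrees separately from relatives the index case is willing to invite, so the paragraph could say which of the two the 2.5 refers to.

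**Conclusion.** The point holds for the index-case chain. The 70%, 495 and 305 cannot all be right as written. The discrepancy is 59 approaches (about 14%), or equivalently 61.6% against 70% acceptance, or an unstated loss of about 12%. This rests only on the article's own figures and on reading its sentence as the derivation it claims to be. Which figure should give way is open. If the true planning acceptance were 61.6%, writing 436 would imply a yield of only 436 × 0.616, about 269.

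The relatives' figure of 381 is correct for 305 index cases.

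A reader might also take 70% as a success criterion, so that 62% would count as failure. The article sets no such threshold; the response rates are listed as feasibility measures without a cut-off. Severity is therefore minor: a stated planning figure needs correcting, and neither the design nor the analysis is affected.

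**What to change.** Check the sentence against the calculation behind Figure 1, then state one consistent chain. Any one of these is sufficient:

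- keep 70% and write 436 approached for 305, or 429 for 300;
- keep 495 approached for 305 and state acceptance of about 62%;
- keep 495, 70% and 305, but label 495 as the number selected before a further loss of about 12%, and name that loss.

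Use one target, 300 or 305, throughout. Leave 381 relatives if 305 is kept, and write 375 if 300 is chosen. Optionally, add a clause saying whether the 2.5 relatives per index case is net of the index case's willingness to invite them.

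The cost is a change of wording and at most two recalculated figures. Figure 1 should be checked for agreement. No change to design, recruitment procedure or analysis is needed.

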### Recruitment Procedures for Index Cases

Participating Swiss clinical sites will record the total number of mutation-harboring families for HBOC or LS. A dedicated staff person at each clinical site, the site coordinator, will identify eligible index cases (ie, first person in the family identified as carrying a germline pathogenic variant associated with HBOC or LS), determine whether they can be contacted or not, and initiate and monitor the recruitment process. Selection of mutation-harboring families from each clinical site will involve the following steps:

Each site creates a list with IDs (eg, 001…, 350) corresponding to each index case and a family with a pathogenic variant.The ID list is sent to the PI, who selects approximately 35% of cases with the assistance of a computer-generated random list. Identifiable information is not released until the index case accepts participation through signing an informed consent form.Site coordinators retrieve the medical charts of selected index cases and decide whether the cases can be contacted by determining living status and residence.If the index case is not available, then site coordinators identify first-degree relatives, who have also been identified through genetic testing as carriers of the familial pathogenic variant, and randomly (computer-generated list) select one of them.Steps 3 and 4 are repeated until an index case who can be the initial contact person for the family is identified. If this process yields no results, the next family is selected.All information obtained from each step is recorded, including minimum information for index cases. Minimum information includes demographics (age, gender), clinical history (tumor type, age at diagnosis, stage), and genetic testing results (including MSI and IHC tumor testing for LS patients) and is obtained from medical records. Index cases are recruited to the CASCADE study by the medical director of the respective site.

Index cases will be mailed an information letter, two copies of the informed consent form, two copies of a participation refusal form, and a stamped self-addressed envelope to return their response to the clinical site. Index cases will be informed about the objectives of the CASCADE study, participation requirements, the study plan, confidentiality, and associated risk and benefits through the informed consent form, which explicitly requires their agreement to (1) complete the CASCADE survey, (2) contact one or more of their blood relatives for the study, (3) be contacted once a year for 5 years and provide updated information about their health, and (4) participate alone or with a blood relative in a focus group. Index cases can participate in all or in some of the above study steps. The information letter explains that the minimum requirement for taking part in the CASCADE study is to complete the self-administered survey once. The refusal form asks nonparticipating index cases the reason for their refusal; this information is necessary for the validity of the study.

Site coordinators will determine whether the identified index case can be contacted or not by investigating whether they are alive and whether they live in Switzerland through hospital and civil records. If the recruitment package is returned undelivered, additional address verification methods will be used to locate a new residence. If the index case cannot be contacted a priori, coordinators will determine whether a first-degree relative can be the new index case for the family. Three attempts will be made to contact index cases for each family. If the study receives no response 6 weeks after the third attempt, a new family will be selected to preserve required sample size. Index cases will be recruited to the CASCADE study on a consecutive ongoing basis. Site coordinators will review pedigrees and family history of index cases who accept participation to extract demographic and medical information and to record all blood relatives (first- and second-degree relatives and first cousins). Index cases will be asked to complete a self-administered survey.

When an index case has not received genetic counseling at the participating center, the invitation package for the CASCADE study will be sent by the referring physician. This is necessary because some clinical sites perform only genetic testing and the referring physician is considered the medical person who has direct knowledge of index case’s genetic testing results. Site coordinators and the PI will keep track of the recruitment process. Referring physicians will make three recruitment attempts by mailing a new invitation package every 6 weeks if the index case does not respond to the invitation (either positively or negatively). Contact information (address, telephone, email) of the PI and the medical director will be provided in the information letter, so that index cases can request further information about the study at any point. A signed informed consent will be requested prior to index case’s enrollment as a prerequisite for engagement in the CASCADE study.

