**Selection of eligible index cases**			
	Random selection of families	Each clinical site provides the principal investigator (PI) with a list of the family identifications (IDs) determined by the clinical site as harboring a pathogenic germline variant. The PI randomly selects 35% of family IDs from the list with computer-generated numbers. The number of selected family IDs at each site is based on total number of family IDs at the clinical site and stratification for representative sampling.	No identifiable data for index cases are shared with the PI.
	Identification of eligible index cases	Through pedigrees and family history records, each site coordinator identifies index cases (1st family member to be identified as a carrier of a germline pathogenic variant) and determines whether they can be contacted (ie, alive and living in Switzerland). If an index case cannot be contacted, site coordinators identify 1st degree relatives who carry the familial pathogenic variant, randomly select one of them (computer-generated numbers), and determine whether they can be contacted. The process is repeated until an eligible mutation carrier is identified that can initiate cascade screening in the family.	Clinical sites collect minimal data (except identifiable data) for all index cases, regardless of whether they can be reached or not. Minimum data include gender, age, mutation, cancer type, age at diagnosis, stage, age tested, alive, place of residence, preferred language.

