### Data Analyses

Selection bias will be minimized by random selection of mutation-harboring families in each clinical site from three linguistic regions of Switzerland. Stratification will ensure selection of an equal proportion of index cases from clinical sites that offer genetic services for both syndromes. The study will try to recruit all index cases from clinical sites including fewer than 100 mutation-harboring HBOC/LS families to ensure a representative sample.

All statistical analyses will be conducted in licensed software packages, including Microsoft Excel, SPSS (IBM), and R. For all statistical tests, significance will be set at two-sided alpha=.05. Data values will be examined for legality (within appropriate range) using histograms and box plots and corrected when possible. Descriptive analyses will include calculating means, standard deviations, frequencies, and percentages of variables and participant descriptors. Bivariate analyses (Pearson correlations, chi-square test for differences in proportions, and *t* test for differences in means) will assess associations between demographics and clinical characteristics. Regression analyses will incorporate generalized estimating equations for pairing index cases with their relatives and explore to what extent predictors are in direct, mediating, or moderating relationship to an outcome.

The following comparisons will take place: between index cases and relatives, between HBOC and LS, between men and women, cancer patients versus cancer-free individuals, participants with children versus those with no children, between different age groups and different cancer diagnoses. Data from participants who withdraw will be kept in the study to ensure the internal validity of the study. Missing data from multi-item scales will be addressed with multiple imputations using R software if they exceed 5% of observations and if they are less than 25% for each specific scale. Scale reliability will be assessed with Cronbach alpha and principle component analyses. Deviations from the planned analyses are not foreseen. The study statistician will review and approve any deviations from the original statistical plan if necessary.

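### Random selection is credited with minimising selection bias, but it governs only who is approached; replacing silent families restores the number, not representativeness, and no listed analysis uses the data held on non-participants

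*Protocol article*

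**What the plan says.** All references are to the protocol article.

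- **Draw.** Table 1 (selection of eligible index cases): "The PI randomly selects 35% of family IDs from the list with computer-generated numbers". Under Recruitment Procedures for Index Cases, a family without a contactable carrier is passed over: "If this process yields no results, the next family is selected".
- **Replacement for silence.** Same section: "Three attempts will be made to contact index cases for each family", and then "If the study receives no response 6 weeks after the third attempt, a new family will be selected to preserve required sample size".
- **Claim about bias.** Data Analyses: "Selection bias will be minimized by random selection of mutation-harboring families in each clinical site from three linguistic regions of Switzerland". The same paragraph adds stratification at sites serving both syndromes and an attempt to recruit every index case at sites with under 100 families.
- **Data on non-participants.** Table 1: "Clinical sites collect minimal data (except identifiable data) for all index cases, regardless of whether they can be reached or not". These cover sex, age, variant, tumour type and stage, ages at diagnosis and testing, vital status, residence and language. Active refusers are also asked why: "The refusal form asks nonparticipating index cases the reason for their refusal; this information is necessary for the validity of the study".
- **Expected participation.** Sample and Sample Size gives about 70% acceptance, and 495 index cases approached to obtain 305.
- **Planned analyses.** Data Analyses lists descriptive, bivariate and regression analyses and a set of subgroup comparisons. All are among participants. It adds that no departure from them is expected.
- **Feasibility outcome.** Outcomes includes the index cases' survey response rate among the measures of registry feasibility.

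**The concern.** A random draw protects against bias in choosing whom to approach. Selection that happens afterwards, when some index cases consent and others refuse or stay silent, is untouched by it. The same holds for stratification and for taking all cases at small sites. Drawing another random family in place of a silent one adds, on average, another family with the same chance of silence. The final sample therefore consists of those who respond, whatever its size.

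Two results are exposed. The Aim 1 estimates (surveillance, psychosocial needs, communication, quality of life) are meant to describe carriers known to the clinics but would describe willing carriers. The response rate, a feasibility outcome, depends on whether replaced families stay in its denominator, which the article does not state. The data that would let the team examine both are already being collected.

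**Working it through.** **1. The plan's own participation figures**

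Inputs: acceptance about 70%; 495 approached; 305 obtained (Sample and Sample Size).

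- Number to approach at 70%: 305 / 0.70 = 435.7, so 436. The stated 495 is not reproduced.
- Conversely, 495 x 0.70 = 346.5, not 305.
- Acceptance implied by the two counts: 305 / 495 = 61.6%.

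Non-participation among those approached is thus 30% as stated, or 1 - 0.616 = 38.4% from the counts. An extra step of about 88% (0.616 / 0.70), such as contactability, would reconcile them, but the text gives none and Figure 1 is not available. The mismatch is a separate matter; both values are carried forward as a range.

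**2. Bias from non-participation**

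Bias = (non-participation share) x (participant value minus non-participant value). The difference is assumed; the article gives none.

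| Assumed difference | 30% not taking part | 38.4% not taking part |
|---|---|---|
| 10 points | 0.30 x 10 = 3.0 | 0.384 x 10 = 3.8 |
| 20 points | 0.30 x 20 = 6.0 | 0.384 x 20 = 7.7 |

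Sampling error for comparison: 1.96 x sqrt(0.25 / 305) = 5.6 points at n = 305 (proportion 50%, simple random sampling).

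With an assumed 60% in participants, the half-width is 1.96 x sqrt(0.6 x 0.4 / 305) = 5.5 points. By normal approximation, a nominal 95% interval then covers the value for all approached carriers as follows:

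| Non-participants | 70% response | 61.6% response |
|---|---|---|
| 50% (10 points lower) | about 81% | about 72% |
| 40% (20 points lower) | about 43% | about 22% |

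**3. What replacement changes**

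Suppose 305 families are drawn and 70% respond.

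- Without replacement: 305 x 0.70 = 213.5 participants, half-width 1.96 x sqrt(0.24 / 213.5) = 6.6 points.
- Filled to 305: half-width 5.5 points.

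The response share does not enter the bias differently in the two cases, so the bias is the same. Replacement buys precision only.

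**4. The response-rate denominator**

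Illustration: 495 approached, 305 take part, 190 do not, and half of those (95, assumed) are silent.

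- All kept in the denominator: 305 / 495 = 61.6%.
- Silent families dropped: 305 / 400 = 76%.

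The article does not say silent families would be dropped. The example shows only how much the unstated choice could matter.

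**5. What weighting on the minimum data could do**

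Illustration (all assumed): two equal groups defined by a recorded variable, response 80% and 60% (70% overall), outcome 70% and 40%.

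- True value: 0.5 x 0.70 + 0.5 x 0.40 = 55%.
- Unweighted among participants: (0.5 x 0.80 x 0.70 + 0.5 x 0.60 x 0.40) / 0.70 = 0.40 / 0.70 = 57.1%.
- Weighted by inverse probability of response: 55%.

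This works because the outcome differs only by the recorded variable. Differences within those groups would remain.

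**The case against.** The strongest defence is that a condensed article may leave non-response methods to an analysis plan that is not shown, and that any consent-based survey enrols only responders. The first part stands: the lack of a weighting method would be weak ground by itself. The second is true, but it does not rescue a statement that credits the sampling design with minimising selection bias when 30% to 38% are expected not to take part.

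A reader might infer several stronger things that the document does not support:

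- **That replacement creates or enlarges the bias.** It does not; the bias is the same without it. The article claims only that replacement keeps the sample size, which is correct.
- **That replacement hides the shortfall.** Mailing and response dates, attempts, response rates and refusal reasons are logged, and the response rate is an outcome. Only the denominator is left unstated.
- **That the plan relies on the draw alone.** Stratification, full sampling of small sites, repeated attempts and address checks are also there. The last two can raise response; the others act before it.
- **That the rule cannot be carried out at small sites.** All index cases are sought there, so no undrawn family may remain, but the article does not say a replacement must come from the same site. This is an ambiguity, not a contradiction.
- **That unmet need is understated.** It is plausible that silent carriers have less surveillance or family communication, but nothing in the article shows it.

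The 30% to 38% also includes active refusers, whereas the written replacement rule covers silence. The silent share is not given, so none of the bias in the working is attributable to the rule itself.

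**Conclusion.** The concern holds in a limited form. The measures credited with minimising selection bias act on who is approached. By the article's own figures about a third of approached index cases will not take part, replacement leaves the resulting bias where it was, and no listed analysis or comparison uses the minimum data to examine it. Followed as written, the Aim 1 estimates describe participants while the text presents selection bias as dealt with by design.

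The bias could be smaller than sampling error (3 to 4 points for an assumed 10-point difference) or somewhat larger (6 to 8 points for 20), against a half-width of about 5.6 points. These sizes rest wholly on assumed differences, and the direction is unknown. This is a worthwhile, inexpensive improvement, not a flaw that undermines the study.

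**What to change.** 1. In Data Analyses, limit the statement on selection bias to the choice of families to approach, and say that non-participation is examined separately.
2. Define the index-case response rate with every eligible family drawn, original and replacement, in the denominator. Flag each replacement and why it was made (no contactable carrier or no response).
3. Compare participants, active refusers and silent index cases on the minimum data.
4. As a sensitivity analysis, model participation on the minimum data and report Aim 1 estimates weighted by the inverse probability of response beside the unweighted ones.
5. State how the replacement rule applies at sites with under 100 families, where all index cases are already sought.

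The cost is analysis time and a few sentences, with no new data collection. Weights widen the intervals slightly. They correct only for recorded variables; family communication and attitude to testing are not among them, so the weighted results should be presented as a partial check.
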